**Objective:**

We aim to conduct a preliminary evaluative study comparing the sensitivity, specificity, and reliability of the BrainFx Screen (referred to as SCREEN hereafter), a novel digital tool designed to assess functional competence and detect early signs of cognitive impairment, with the Quick Mild Cognitive Impairment, a validated and highly sensitive tool that detects MCI in the older adult population. We will also investigate the perceived usefulness and integration of the SCREEN into primary care practice to identify demonstrable impacts on clinical workflow and health care providers’ (HCP) perceptions of its success as a screening tool. Patients’ perceptions of completing the SCREEN and its impact on their quality of life will also be explored.

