The patients’ first appointment will take approximately 45-60 minutes (to account for onboarding), and all subsequent appointments (up to 4 screening test pairs, depending on the patient’s study entry date) will take approximately 45 minutes to complete. Rolling recruitment of patients will occur over an 18-month period and will end when a minimum of 2 and a maximum of 4 SCREEN-Qmci test pairs are completed every 12 weeks. In older adults, with no diagnosis of MCI or dementia, measures of cognitive abilities, including verbal fluency, attention, and intelligence [100], and measures of executive functioning [101] remain stable for anywhere from 4 to 8 weeks or from 1 to 5 years between test and retest (controlling for the effects of normal aging [100]). To date, there are no clear guidelines on the optimal time between tests [102,103]. Streiner [104] recommends longer periods to avoid recall bias. Furthermore, greater practice effects are experienced with shorter test-retest intervals [62]. The 3-month interval was therefore selected to minimize such confounds and is justified given the stability of the constructs under investigation. A randomization process will determine the order of screen administration at each visit. The Qmci will be administered using a pen and paper. HCPs will be provided with identical tablets, preloaded with the SCREEN app software.

The GAS-10 will be administered just before and immediately after the administration of the first MCI screen (eg, the SCREEN) and immediately followed by the administration of the second MCI screen (eg, the Qmci) at each appointment. After completing the 2 MCI screens, the HCP will manually calculate the results for the Qmci, log in to the BrainFx portal to retrieve the SCREEN report, and review both sets of results with the patient. The Qmci cut-off score for distinguishing MCI from normal cognition is ≤67/100 [88]. The SCREEN does not include scoring guidelines for a cut-off score but identifies whether a score on any of the 7 tasks is an *area of challenge*.

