To determine the sensitivity and specificity of the SCREEN in comparison with the Qmci, the results of both screens will be classified in binary format as healthy or not healthy, where *healthy* denotes SCREEN=no areas of challenge in all 7 activities and Qmci≥67 and *unhealthy* denotes SCREEN=1 or more areas of challenge and Qmci≤67. Consistent with consensus guidelines for screening for cognitive impairment [37,49,50], the research protocol will also require HCPs to refer patients to their primary care physician for further evaluation if they receive an abnormal score on the Qmci or significant concerns on the SCREEN. The SCREEN does not have a standardized cut-off score that can be used to classify results as abnormal. Therefore, in consultation with and on the recommendation of the SCREEN developers, for the purpose of the research protocol, a set of cut-off scores was developed to classify SCREEN results as normal (zero areas of challenge), some concerns (≤3 areas of challenge), or significant concerns (≥4 areas of challenge). All HCPs in this study will be OTs who are trained to assess individuals’ abilities or disabilities through the use of standardized testing and functional observation. As a result, the study protocol includes a condition that referral decisions for physician oversight or further testing are the purview of the HCP and their clinical judgment. This became the proxy gold standard for a positive screen in this research study.

Following the review of the results at each appointment, the HCP will provide patients with a handout that summarizes recommendations for supporting cognitive health. If the SCREEN identifies any *areas of challenge,* the patient will also receive a handout developed by BrainFx containing tailored strategies to strengthen brain health and manage deficits in those areas.

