#### Descriptive and Inferential Analysis

Descriptive data will be described using frequencies and percentiles and compared using the chi-square test or Fisher exact test as necessary. Continuous data will be analyzed for central tendency and variability; categorical data will be presented as proportions. Normality will be tested using the Shapiro-Wilk test, and nonparametric tests will be performed using the Mann-Whitney U test*.* Statistical significance will be considered at a *P* value of .05, with 90% CI provided where appropriate. We powered the exploratory analysis to validate the SCREEN using an estimated effect size of 12%, with the understanding that Canadian prevalence rates are not available [29], and determined that we needed at least 114 participants. For test-retest reliability, using 90% power and a 5% type 1 error rate, we will require a minimum of 58 test results.

MCI test outcome data will be coded into a binary format of *healthy* or *unhealthy* (where unhealthy indicates a positive result on the test, ie, 1 or more *areas of challenge* on the SCREEN results, or a score of ≤67/100 on the Qmci) to account for the difference in categorical versus continuous outcome variables. For this reason, sensitivity and specificity will be determined using cross-tabulation rather than using the area under the curve using receiver operating characteristic curves. A principal component analysis with varimax rotation will be used to better understand the derivation of components’ contribution to screen test outcomes and to explore the differences between a conventional MCI screen (Qmci) and one that is intended to be more ecologically valid by assessing functional impairment (SCREEN). Binary logistic regression will examine the effects of variables such as age, education, self-reported comfort with technology, anxiety before and after completing the MCI tests, and sleep levels on the results. The internal consistency of both the SCREEN and Qmci will be assessed using Cronbach α. Test-retest reliability, the ability of a measurement instrument to reproduce results on 2 or more occasions (ceteris paribus), will be assessed using an intraclass correlation coefficient [106].

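### The protocol compares SCREEN accuracy with the Qmci but also names the clinician's referral decision as proxy gold standard; referral depends on both screens and cannot serve as the reference for either

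*Protocol article*

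**What the plan says.** The Objective in the abstract speaks of "comparing the sensitivity, specificity, and reliability of the BrainFx Screen" with the Qmci. In Psychometric Evaluation, the paragraph on classifying results opens "To determine the sensitivity and specificity of the SCREEN in comparison with the Qmci" and dichotomises both screens. The SCREEN is positive with one or more areas of challenge, and the Qmci is positive at 67 or below.

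The same paragraph turns to referral: "the research protocol will also require HCPs to refer patients to their primary care physician for further evaluation if they receive an abnormal score". Two findings count as triggers: a Qmci in the abnormal range, or a SCREEN report in the most serious of its three categories. That category is defined later in the paragraph: "or significant concerns (≥4 areas of challenge"). The text then adds that "referral decisions for physician oversight or further testing are the purview of the HCP and their clinical judgment", and closes: "This became the proxy gold standard for a positive screen in this research study". The natural antecedent of that last sentence is the referral decision.

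Earlier in the section, the provider scores the Qmci by hand and is then to "log in to the BrainFx portal to retrieve the SCREEN report, and review both sets of results with the patient". Descriptive and Inferential Analysis says that "sensitivity and specificity will be determined using cross-tabulation rather than using the area under the curve". It codes the SCREEN and the Qmci as binary but does not say which variable is the reference. Limitations mentions proxies of the kind that are validated, sensitive tests for the same condition. That describes the Qmci and not a referral.

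**The concern.** The reference standard decides what sensitivity and specificity mean. One paragraph points to two candidates, and the analysis section does not choose between them.

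The second candidate is also unsuitable. The person who decides on referral has both results in hand, and the SCREEN is itself one of the required triggers. A patient referred on four or more areas of challenge has at least one, so is SCREEN-positive by definition. The test under evaluation would then form part of its own reference (incorporation bias), and the reference would be read unblinded. The Qmci is a trigger too, so its accuracy against referral would be no more independent.

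The study is meant to help the developers decide whether controlled testing is warranted (abstract, Conclusions). Accuracy figures that cannot be interpreted would feed that decision.

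**Working it through.** The plan gives no accuracy figure to reproduce, so the check is on direction first and then on an illustrative size.

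**1. Direction under the stated triggers.** Let TP, FN, FP and TN be the counts for SCREEN (≥1 area) against the Qmci (≤67). Suppose every Qmci-positive patient is referred, plus x Qmci-negative patients with four or more areas, and nobody else. All x patients are SCREEN-positive, so they move from FP to TP:

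- Sensitivity: TP/(TP+FN) becomes (TP+x)/(TP+FN+x), which is higher when x>0 and FN>0.
- Specificity: TN/(TN+FP) becomes TN/(TN+FP−x), which is higher when x>0 and TN>0.
- Qmci against referral: every patient not referred is Qmci-negative, so specificity is 100%. Sensitivity is (TP+FN)/(TP+FN+x).

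In 100,000 randomly generated tables, SCREEN sensitivity or specificity was never lower under this rule than against the Qmci.

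**2. Illustrative size.** From the protocol: 114 participants, 7 activities, an area of challenge at 1 SD or more below the mean, and positivity at ≥1 and referral at ≥4 areas. Assumed: 20% Qmci-positive, normal activity scores in a one-factor model with correlation 0.3, and a SCREEN unrelated to the Qmci. Numerical integration gives P(≥1 of 7) = 56.2% and P(≥4 of 7) = 6.74%. The expected counts are:

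- Qmci-positive 0.20×114 = 22.8, giving TP 12.8 and FN 10.0.
- Qmci-negative 91.2, giving FP 51.2 and TN 40.0.
- x = 91.2×0.0674 = 6.15.

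| Reference | SCREEN sensitivity | SCREEN specificity |
|---|---|---|
| Qmci ≤67 | 12.8/22.8 = 56.2% | 40.0/91.2 = 43.8% |
| Referral, triggers only | 18.96/28.95 = 65.5% | 39.97/85.05 = 47.0% |
| Referral, triggers plus 5 patients clear on both screens | 18.96/33.95 = 55.8% | 34.97/80.05 = 43.7% |

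The second row shows an apparent gain of 9.3 and 3.2 points for a SCREEN with no association with the Qmci. The third row shows that five judgment referrals out of 40 doubly clear patients remove it. Under triggers only, the Qmci has sensitivity 22.8/28.95 = 78.8% and specificity 100%.

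**3. Range under triggers only.** Write a1 and a4 for P(≥1) and P(≥4), and q for the Qmci-positive rate. Then sensitivity against referral is [q·a1+(1−q)·a4]/[q+(1−q)·a4], and specificity is (1−a1)/(1−a4).

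| Correlation | a1, a4 | Sensitivity rise at q = 10/20/40% (points) | Specificity rise (points) |
|---|---|---|---|
| 0 | 70.2%, 1.5% | 3.5 / 1.7 / 0.6 | 0.4 |
| 0.3 | 56.2%, 6.7% | 16.6 / 9.3 / 4.0 | 3.2 |
| 0.5 | 47.5%, 9.9% | 24.8 / 14.9 / 6.8 | 5.8 |

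**4. Judgment can also push upward.** Assume 12% Qmci-positive, SCREEN 50%/50% against the Qmci, and 10% of Qmci-negatives at four or more areas. Triggers only give sensitivity (0.06+0.088)/(0.12+0.088) = 71.2% and specificity 0.44/0.792 = 55.6%. If only half of the Qmci-positive patients with a clear SCREEN are referred, sensitivity is 0.148/0.178 = 83.1% and specificity 0.47/0.822 = 57.2%.

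**The case against.** Four points can be made on the other side.

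*The comparison with the Qmci may be head to head, with referral as the single reference for both screens.* The wording allows this, and it would remove the contradiction. It does not help the plan, because the reference would then contain both tests being compared. The Limitations text also points to a validated test as the proxy.

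*If the cross-tabulation is simply SCREEN against Qmci, the sentence is loose wording with no effect.* This is fair as far as it goes. Only the two screens are coded as binary in the analysis section, which makes the Qmci the likelier reference. But the section does not say so, and the one explicit naming of a gold standard points to referral.

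*Judgment breaks the direction.* This stands. A reader might infer that a referral reference must favour the SCREEN. The document does not support that. It leaves referral to clinical judgment by occupational therapists, who also observe function. Limitations expects people worried about their cognition to self-select, so referral of patients clear on both screens is plausible. The third row of the worked case shows the gain gone.

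*The Qmci benefits too.* This also stands. Under the triggers alone, SCREEN figures rise relative to using the Qmci as reference. The SCREEN does not thereby come out ahead of the Qmci, which scores 78.8%/100% in the same case against 65.5%/47.0%.

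**Conclusion.** The concern holds in conditional form. The protocol does not settle which reference applies, and the one it calls a gold standard is decided unblinded and partly triggered by each screen under study. It cannot serve as the reference for the accuracy of either. That conclusion follows from the text and needs no assumed figure.

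The direction is proved only if referral follows the stated triggers and nothing else. Once judgment enters, the SCREEN figures can move either way. The size cannot be derived from the document. The rise of 0.6 to 24.8 points in sensitivity and 0.4 to 5.8 in specificity rests on assumed Qmci-positive rates, an assumed correlation model, no true association and triggers-only referral. It also uses the planned 114 participants for the counts, although data collection stopped early. It shows that the effect may be negligible or large, and it is not an estimate.

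Nothing in the document shows that accuracy against referral has been or will be computed. The harm arises if the gold standard sentence is followed or reported.

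**What to change.** The abstract describes data analysis as in progress, so this can be settled before reporting.

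1. State that Qmci ≤67 is the reference for SCREEN sensitivity and specificity, and name it as such for the cross-tabulation.
2. Replace the gold standard sentence with: Referral is a clinical-management outcome informed by both screens and is not used as the reference for sensitivity or specificity.
3. From the patient encounter form, which already records screen results and referrals, tabulate trigger met (Qmci ≤67 or ≥4 areas of challenge) against referred or not. State which referral rule the providers worked under.
4. If any accuracy figure against referral is or has been reported, label it secondary and disclose that referral depends on both screens. This keeps the record honest if referral was in fact used.

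The cost is two sentences and one descriptive table, with no new data. The downside is a little extra analysis and possibly less favourable figures for the SCREEN.

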#### Perceived Usefulness and Clinical Workflow Integration

Semistructured, in-depth interviews will be conducted, in person or by telephone, with HCPs, executive directors, and a subset of patients and their care partners throughout the study. Interviews will be audio-recorded and transcribed verbatim. Data collection will be guided by the *TTF theoretical model*, which emphasizes the importance of the fit between technologies and users’ tasks in creating a perceived net benefit to use [89,105] (Figure 2). Standard questions to capture demographics, attitudes, and experiences data will also be asked at the beginning of each interview.

HCPs will complete a TTF questionnaire (Textbox 2) as part of their entry or exit interviews with a member of the research team, which will be scheduled 3 months after they enter the study and again within 1 month after they exit the study.

**Figure 2 figure2:**
[figure not shown]
Task Technology Fit model.

Task Technology Fit questionnaire. Task Technology Fit questionnaire response options are as follows: 1=entirely disagree, 2=mostly disagree, 3=somewhat disagree, 4=neither agree nor disagree, 5=somewhat agree, 6=mostly agree, and 7=entirely agree.
**Technology enhancements**
The quality of the information I receive from the BrainFx SCREEN and Report is enough to meet my clinical needs.The BrainFx SCREEN and Report provides me with the right data I need to better support patients and caregivers.I am able to quickly locate the results of the BrainFx SCREEN on a patient chart.The data elements on the BrainFx Report are easy to understand or it is easy to find out.
**User satisfaction**
Technical support to access the BrainFx app was always available when I needed it.I can count on the BrainFx system to be “up and running” and available when I need it.The tablets were subject to unexpected or inconvenient downtimes, which makes it harder for me to do my work.The BrainFx app was subject to frequent problems.It was easy to learn the BrainFx system.
**Task characteristics**
I frequently deal with nonroutine cases of older adults with cognitive issues.I frequently deal with routine cases of older adults with cognitive issues.Identifying cases of mild cognitive impairment usually takes more than one clinician.Sharing relevant and timely information with other care providers is important when diagnosing cognitive impairment.
**Utilization**
The BrainFx system was convenient and easy to use.There was not enough training for me on how to administer the BrainFx SCREEN using the tablets.There was not enough training for me on how to use the BrainFx Report.BrainFx support took an interest in helping me to solve problems to avoid disruptions to my workflow.
**Perceived net benefits to use**
My overall effectiveness in detecting mild cognitive impairment increased when I used the BrainFx SCREEN and Report.My ability to target interventions for individual patients and their needs was improved with the BrainFx SCREEN and Report.My ability to target interventions for individual caregivers and their needs was improved with the BrainFx SCREEN and Report.I waste less time interpreting test results and preparing interventions with BrainFx SCREEN and Report.I spend less time writing up charting cognitive test results with the BrainFx SCREEN and Report.The BrainFx SCREEN and Report provide better information to patients and their caregivers.The quality of my follow-up recommendations to patients and caregivers has improved with my use of the BrainFx SCREEN and Report.

### Statistical and Analytic Plan

Descriptive and inferential analyses will be conducted using SPSS Statistics for Windows, Version 26 (IBM Corp). Qualitative analysis will be conducted using NVivo version 12 (QSR International Pty Ltd).

#### Descriptive and Inferential Analysis

Descriptive data will be described using frequencies and percentiles and compared using the chi-square test or Fisher exact test as necessary. Continuous data will be analyzed for central tendency and variability; categorical data will be presented as proportions. Normality will be tested using the Shapiro-Wilk test, and nonparametric tests will be performed using the Mann-Whitney U test*.* Statistical significance will be considered at a *P* value of .05, with 90% CI provided where appropriate. We powered the exploratory analysis to validate the SCREEN using an estimated effect size of 12%, with the understanding that Canadian prevalence rates are not available [29], and determined that we needed at least 114 participants. For test-retest reliability, using 90% power and a 5% type 1 error rate, we will require a minimum of 58 test results.

MCI test outcome data will be coded into a binary format of *healthy* or *unhealthy* (where unhealthy indicates a positive result on the test, ie, 1 or more *areas of challenge* on the SCREEN results, or a score of ≤67/100 on the Qmci) to account for the difference in categorical versus continuous outcome variables. For this reason, sensitivity and specificity will be determined using cross-tabulation rather than using the area under the curve using receiver operating characteristic curves. A principal component analysis with varimax rotation will be used to better understand the derivation of components’ contribution to screen test outcomes and to explore the differences between a conventional MCI screen (Qmci) and one that is intended to be more ecologically valid by assessing functional impairment (SCREEN). Binary logistic regression will examine the effects of variables such as age, education, self-reported comfort with technology, anxiety before and after completing the MCI tests, and sleep levels on the results. The internal consistency of both the SCREEN and Qmci will be assessed using Cronbach α. Test-retest reliability, the ability of a measurement instrument to reproduce results on 2 or more occasions (ceteris paribus), will be assessed using an intraclass correlation coefficient [106].

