#### Psychometric Evaluation

Data collection for the psychometric evaluation study will take place in person at the patients’ respective FHT. Standard operating procedures have been developed for the research study, which will be followed by the research team and HCP staff trained in the study protocol and administration of all data collection tools. A member of the research team will observe at least one in-clinic HCP data collection visit to confirm adherence to the protocol and training procedures.

To assess the reliability and perceived usefulness of the SCREEN, depending upon when a patient enters the study, they may repeat the screening protocol up to 4 times. Each visit is structured around the administration of 2 MCI screens; the *GAS-10* [81,82]; and a series of questions that measure the patient’s use of technology, change in their general health and well-being, or any interactions with the health care system related to MCI that occur in the 3 months since their last appointment. The HCP will be required to complete a patient encounter form at each appointment, which includes a summary of the patient’s MCI screen results, any referrals, and their responses to these questions.

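### Mann-Whitney U, an independent-groups test, is the only nonparametric test named, although GAS-10 change is to be assessed within the same patients

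*Protocol article*

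**What the plan says.** The tests are set out in the protocol article under Descriptive and Inferential Analysis. After a Shapiro-Wilk check of normality, "nonparametric tests will be performed using the Mann-Whitney U test". Descriptive data are to be "compared using the chi-square test or Fisher exact test as necessary". The significance rule is a P "value of .05, with 90% CI provided where appropriate". No signed-rank, paired t, McNemar or repeated-measures comparison is named.

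The same section plans sensitivity and specificity by cross-tabulation and test-retest reliability by an intraclass correlation coefficient. It also plans principal component analysis, Cronbach alpha and binary logistic regression.

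The data structure is described under Psychometric Evaluation. "Each visit is structured around the administration of 2 MCI screens", and "The GAS-10 will be administered just before and immediately after the administration of the first MCI screen". Patients contribute two to four such visits, 12 weeks apart, and the order of the screens is randomized at each visit. The Measures section on the 10-item GAS gives, as one purpose of the scale, the assessment of change in anxiety ratings once the screen is done and from visit to visit.

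**The concern.** A before-and-after GAS-10 comparison, or one between visits, sets two scores from the same person side by side. Mann-Whitney assumes two independent groups. It ignores the correlation within patients and so uses too large a standard error for the difference whenever that correlation is positive.

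The nonparametric branch may well apply. The GAS-10 is bounded from 0 to 30, and the article does not expect high anxiety unrelated to testing, so scores bunched near the lower end are plausible.

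The risk is that a small or moderate change in anxiety comes out as non-significant and is read as evidence of no change, when the test had little power to show one. The same would apply to visit-to-visit shifts in screen scores, if those are tested. The article discusses practice effects but does not assign them a test.

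**Working it through.** **Inputs**
- From the article: significance level .05 (taken as two-sided, since sidedness is not stated). The validation sample size comes from the statement that the authors "determined that we needed at least 114 participants". The minimum for test-retest reliability is 58 test results. The number 58 is used below only as an illustrative smaller number of pairs.
- Assumed, because the article does not give them: within-patient correlation ρ from 0 to 0.85, change d from 0.2 to 0.5 SD, and normal scores.

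The article gives no power figure for a within-patient change, so there is none to reproduce. The figures 114 and 58 are not in dispute here.

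**Large-sample approximation** (n pairs, unit SD)
- Standard error that an unpaired test assumes: √(2/n).
- Actual standard error of the mean difference: √(2(1−ρ)/n), smaller by a factor √(1−ρ).
- Unpaired power ≈ P(Z > (1.96 − d/√(2/n)) / √(1−ρ)).
- Paired power ≈ P(Z > 1.96 − d/√(2(1−ρ)/n)).

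For n = 114, d = 0.2, ρ = 0.7:
- √(2/114) = 0.1325, so d/SE = 1.51. √0.3 = 0.548.
- Unpaired: (1.96 − 1.51)/0.548 = 0.82, power about 21%.
- Paired: 0.2/(0.1325 × 0.548) = 2.76, and 1.96 − 2.76 = −0.80, power about 79%. The rank test is slightly less efficient than this mean-based figure.

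**Simulation of the two rank tests** (4,000 runs per row, correlated normal pairs, two-sided 0.05)

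| n | ρ | Change (SD) | Mann-Whitney | Signed-rank |
|---|---|---|---|---|
| 114 | 0 | 0.2 | 30% | 31% |
| 114 | 0.3 | 0.2 | 28% | 41% |
| 114 | 0.5 | 0.2 | 25% | 55% |
| 114 | 0.7 | 0.2 | 19% | 76% |
| 114 | 0.5 | 0.3 | 64% | 88% |
| 114 | 0.7 | 0.3 | 67% | 98% |
| 114 | 0.5 | 0.5 | 99% | 100% |
| 58 | 0.5 | 0.3 | 30% | 60% |
| 58 | 0.7 | 0.3 | 26% | 81% |
| 58 | 0.7 | 0.5 | 88% | 99.8% |

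With no true change, Mann-Whitney rejects in 0.5% to 0.7% of runs at ρ = 0.5 and in about 0.1% or fewer at ρ = 0.7, against a nominal 5%. The signed-rank test stays near 5%.

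**Which analyses are affected**
- GAS-10 change within a visit and between visits: a stated aim, paired data, and no paired test named. Affected.
- Sensitivity and specificity: the cross-tabulation sets each patient's SCREEN result against the same patient's Qmci result. Not affected.
- Test-retest reliability: the intraclass correlation is a within-patient measure. Not affected.
- SCREEN versus Qmci positivity rates: the article plans no such test. If one were added, an unpaired chi-square would lose power in the same way. For example, with 30% versus 18% positive, n = 114 and an assumed phi of 0.5, power is 60% against 87% for McNemar's test.

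**The case against.** The strongest reply is that the named tests have proper uses in this study. Screen order is randomized, so a comparison of GAS-10 change scores between SCREEN-first and Qmci-first patients at one visit is a between-patient contrast, and Mann-Whitney is valid for it. Sites and patient subgroups give others. A condensed article may also leave the choice of paired tests to a fuller plan. The first part stands and limits the point. The second stands only in part: the article does not merely stay silent, because it fixes the nonparametric test while stating a within-patient aim.

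A reader might infer more than the document supports:
- *That the main comparisons rest on independent-group tests.* They do not. The sensitivity and specificity cross-tabulation and the intraclass correlation keep the pairing.
- *That chi-square or Fisher will be used to compare SCREEN and Qmci positivity.* The article attaches those tests to descriptive data and plans no test of positivity rates.
- *That real changes would be missed.* The loss depends on an unstated correlation and effect size. It is nil at zero correlation and small for a 0.5 SD change with 114 pairs.
- *That the error favours the SCREEN.* The GAS-10 brackets whichever screen comes first, so a missed pooled change in anxiety does not favour one screen over the other.

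**Conclusion.** The point holds for within-patient GAS-10 change, and for visit-to-visit score changes if they are tested. For these, the named nonparametric test does not match the paired data. For changes of 0.2 to 0.3 SD and correlations of 0.5 to 0.7, the simulated power loss runs from about 24 to 57 percentage points with 114 pairs (88% − 64% = 24; 76% − 19% = 57).

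The size rests on assumed correlations, effect sizes and normal scores. The direction needs only a positive within-patient correlation. That is likely for the GAS-10, because each rating covers the past week and the two ratings at a visit bracket a single screen. The main accuracy and reliability results are untouched, so this is a modest correction to a supporting analysis.

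**What to change.** In Descriptive and Inferential Analysis, state the test by type of comparison:
- Within-patient change (GAS-10 before and after the first screen, and GAS-10 or screen scores from visit to visit): Wilcoxon signed-rank, or paired t where the differences are roughly normal, with a confidence interval for the paired difference. Where more than two visits are analysed together, a mixed model or GEE would serve.
- SCREEN versus Qmci positivity rates, if they are compared: McNemar's test with a paired confidence interval.
- Between-patient comparisons, such as SCREEN-first versus Qmci-first: keep Mann-Whitney, chi-square and Fisher.

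This costs a few lines of analysis text. It needs no new data, visits or patients. The article reports that collection stopped early and that analysis is in progress, so the change is best made before the GAS-10 comparisons are run.

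### Significance is set at P=.05 but intervals at 90%, so conventional two-sided tests and their intervals will disagree whenever P lies between .05 and .10

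*Protocol article*

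**What the plan says.** All of this stands in the Descriptive and Inferential Analysis section of the protocol article. One sentence fixes both levels: significance at a P "value of .05, with 90% CI provided where appropriate". The section does not say whether tests are one- or two-sided, and it describes no equivalence or non-inferiority comparison.

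The tests it names are these:
- Descriptive data are "compared using the chi-square test or Fisher exact test as necessary".
- For non-normal data, "nonparametric tests will be performed using the Mann-Whitney U test".
- Binary logistic regression examines variables such as age, education, comfort with technology, anxiety and sleep. No direction of effect is given.

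Sensitivity and specificity come from a cross-tabulation, and retest reliability from an ICC. No null value or test is attached to either.

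Two sample sizes are given. For the validation analysis the authors worked "using an estimated effect size of 12%, with the understanding that Canadian prevalence rates are not available" and "determined that we needed at least 114 participants". For reliability, "using 90% power and a 5% type 1 error rate", "we will require a minimum of 58 test results".

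**The concern.** A two-sided 90% interval is the counterpart of a two-sided test at .10, or of a one-sided test at .05. It is not the counterpart of a two-sided test at .05. The usual grounds for a 90% interval are a one-sided hypothesis or an equivalence test, and the section states neither. Chi-square on a table larger than 2×2 has no direction, and the other named tests are two-sided by convention.

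On that reading the sentence sets a rule that can give two answers to one question. An odds ratio could be reported as not significant beside an interval that excludes 1. A reader who judges by the interval and a reader who judges by the P value would then reach opposite conclusions from the same row of a table. This is a matter of what the text states, not of detail left to a fuller document.

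**Working it through.** **1. Where test and interval disagree.** The inputs are the .05 and the 90% in the section, plus two-sided testing, which is an assumption. The critical values are z = 1.645 for a 90% interval and z = 1.960 for a two-sided .05 test. A result with |z| between them has P between .05 and .10. It is non-significant, yet its 90% interval excludes the null. Under the null the probability of this is .10 − .05 = .05 per test.

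Illustration: a log odds ratio 1.80 standard errors from zero has P = .072. Its 90% limit lies 1.80 − 1.645 = 0.155 standard errors on the far side of zero from the null. Its 95% limit lies 1.80 − 1.960 = −0.160, so that interval includes the null. The correspondence is exact where test and interval use the same normal statistic, as in a Wald test in logistic regression. It is approximate for the other tests.

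**2. Width.** 1.645/1.960 = 0.839, so the 90% interval is 16% narrower. Equivalently, 1/0.839 = 1.19, so the 95% interval is 19% wider.

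**3. What this means for sensitivity.** Half-width = z × √[p(1−p)/n], with p = 0.80 chosen for illustration. The number of positives is not stated, so two assumed counts are shown:

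| Assumed positives | Source | √[0.16/n] | 90% | 95% |
|---|---|---|---|---|
| 14 | 12% × 114 = 13.7, reading the 12% as a prevalence | 0.1069 | ±17.6 points | ±21.0 points |
| 48 | 42% × 114 = 47.9, the upper figure for MCI after age 60 in the MCI Disorder section | 0.0577 | ±9.5 points | ±11.3 points |

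**4. Could the 114 rest on a 90% interval?** With n = z²p(1−p)/d², p = 0.12 and an assumed margin d = 0.05:
- 90%: 1.645² × 0.12 × 0.88 / 0.05² = 114.3, which matches the stated 114 (115 if rounded up).
- 95%: 1.960² × 0.12 × 0.88 / 0.05² = 162.3, so 163.

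The match is not unique. At 95% with d = 0.06 the formula gives 112.7. A two-sample comparison of 6% with 18% (two-sided 5%, 80% power) gives 114 per arm. The margin is not in the document.

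With n held at 114 and p = 0.12, √(0.12 × 0.88/114) = 0.0304. The half-width is then ±5.0 points at 90% and ±6.0 at 95%.

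**5. Could the 58 rest on a one-sided test?** The usual formula for testing an ICC with k = 2 occasions is n = 1 + 2(zα + zβ)²k / [(ln C)²(k−1)], where C = (1 + kθ0)/(1 + kθ1) and θ = ICC/(1−ICC). Assume ICC 0.70 against 0.85. Both numbers appear in the background text, but neither is stated as a hypothesis. At one-sided 5% and 90% power:
- θ0 = 2.333 and θ1 = 5.667, so C = 5.667/12.333 = 0.4595 and (ln C)² = 0.605.
- n = 1 + 4 × (1.645 + 1.282)²/0.605 = 57.6, so 58.

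Other pairs come close, some of them two-sided: 0.50 against 0.75 at two-sided 5% gives 59.5. The 58 therefore does not settle sidedness.

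**The case against.** The best defence is that 90% may be deliberate. The plan never says its tests are two-sided, and with one-sided 5% tests a 90% interval matches exactly. Both sample sizes can be reproduced with z = 1.645. An article may leave sidedness to a fuller document, and "with 90% CI provided where appropriate" leaves open which analyses get the interval. The study is also described as preliminary and its validation analysis as exploratory, and no decision rule is tied to these intervals.

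Much of this stands as mitigation. The conflict does depend on two-sided testing, and a design built on 90% precision is possible. But both reproductions need assumed inputs and neither is unique, so they do not show intent. One-sided use would also be unusual for the tests named. The two levels are stated together, so the sentence itself needs a reason or a correction.

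Two stronger readings might be inferred, and the document does not support them. The first is that the intervals understate uncertainty. An interval openly labelled 90% is honest at its own level and is simply narrower than the one that pairs with a two-sided .05 test. The second is that sensitivity and specificity would be declared on contradictory evidence. No test is named for them, so an interval has nothing to contradict. Nor does the text fix 14 positives: it calls the 12% an effect size, and positives are set by the Qmci cut-off or by clinical judgment.

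**Conclusion.** The concern holds for the analyses with a named test, meaning the group comparisons and the logistic-regression odds ratios, on the assumption that they are run two-sided. There, any P between .05 and .10 gives a non-significant test beside an interval that excludes the null, which occurs in 5% of tests when there is no effect.

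For sensitivity, specificity and the ICC, 90% is unconventional and unexplained but not contradictory. Its effect is a 16% narrower interval. The absolute size depends on the number of positives, which the document does not give: 3.4 points of half-width with 14 positives and 1.8 points with 48, at 80% sensitivity.

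This does not undermine a preliminary study. It is a clear inconsistency that should be corrected before results are reported.

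**What to change.** Report 95% intervals throughout, using Wilson or exact limits for sensitivity and specificity, and state that tests are two-sided at .05. Keep the 114 and restate the precision it gives: at a proportion of 12%, about ±6.0 points rather than ±5.0, if a 90% interval was its basis. Holding ±5 points at 95% would instead take 163, so the change should not be presented as leaving the sample-size basis untouched.

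If 90% was chosen on purpose, as the counterpart of one-sided 5% tests or as a precision target, say so, give the reason, and list the analyses to which it applies.

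Either route needs no new patients, and the abstract says analysis is still in progress, so it can be done at reporting. The cost of moving to 95% is intervals about 19% wider.
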